## Abstract

**Background:**

Schizophrenia is a persistent psychotic disorder often accompanied by severe disability and premature mortality. New pharmacological treatments are urgently needed. Sodium benzoate, a common food preservative holds potential to be an effective, accessible treatment for schizophrenia, though the optimal dosing and mechanism of action of the compound requires further investigation.

**Methods:**

Individuals with persistent treatment-refractory schizophrenia (*n*=52) will be recruited. Patients will be randomised in a 1:1:1:1 ratio to receive treatment of one of three active doses (1000, 2000 or 4000 mg daily) of sodium benzoate or placebo for 6 weeks duration. The primary outcome measurement is change in the Positive and Negative Syndrome Scale (PANSS) total score. Secondary outcome measurements are PANSS subscales, Global Assessment of Function (GAF), Clinical Global Impression (CGI) and Patient Global Impression (PGI-I). Change in concentrations of peripheral amino acids (D-alanine, L-alanine, D-serine, L-serine, glycine and glutamate), plasma sodium benzoate, plasma catalase, 3-nitrotyrosine, malondialdehyde and high-sensitivity C-reactive protein (hs-CRP) will be determined as tertiary measures.

**Discussion:**

This trial seeks to build upon previous research indicating potential efficacy of sodium benzoate for reduction of symptoms in individuals with treatment-refractory schizophrenia. The trial aims to improve the understanding of the mechanism of action of the compound.

**Trial registration:**

Australian New Zealand Clinical Trials Registry (ANZCTR) ACTRN12621000327886. Registered on 23 March 2021.

## Background

Schizophrenia is a persistent psychotic disorder all too often accompanied by lifelong adverse impact on many facets of life for affected individuals and their families. The symptoms of the syndrome are heterogeneous, frequently categorised into positive, negative and cognitive domains [1]. There is a significant burden of disease attributable to schizophrenia due to its onset commonly occurring in adolescence and young adulthood combined with its persistence, high level of associated disability [2] and excess mortality [3, 4].

### Current therapeutic interventions

Antipsychotics acting through modulation of the dopamine receptor are the most commonly used medicinal treatment for schizophrenia, albeit with high rates of side effects and modest clinical efficacy which often leads to discontinuation [1, 5, 6]. Treatment-refractory schizophrenia is the term used when the illness does not respond to antipsychotic therapy [7]. Although there are no definitive data on the incidence/prevalence of treatment-refractory schizophrenia, a cohort study in the UK (*n*=246) observed that 33% of patients could be classified as treatment-resistant within 5 years of first episode psychosis, and 23% never achieved symptomatic remission [8]. General estimates suggest that up to 40% of people with schizophrenia are treatment-refractory [6]. Clozapine is the recommended medication for those with treatment-refractory schizophrenia, although less than half of people respond and there are significant adverse effects including commonly occurring metabolic syndrome and sedation and uncommon but severe haematological and cardiac side effects [9, 10]. Thus, finding effective and tolerable therapeutics for treatment-resistant schizophrenia is a clinical priority.

### Alternative therapeutic target: the NMDA receptor

The need for novel pharmacological agents has stimulated interest in developing therapeutics which modulate the N-methyl-D-aspartate (NMDA) receptor. Hypofunction of the NMDA receptor has been implicated in the pathophysiology of schizophrenia through clinical, genetic and molecular studies [11–15]. The NMDA receptor consists of 2 subunits, glycine and glutamate. Modulation of the glutamate subunit is limited due to excitotoxicity resulting from elevated glutamate levels [16]. Activation of the NMDA receptor by the amino acids glycine and D-serine results in an improvement in all symptom domains of schizophrenia [17]. However, the use of compounds such as D-serine for treating schizophrenia is inhibited by its limited availability in the central nervous system due to its metabolism by the flavoenzyme D-amino-acid oxidase (DAAO) [18]. Further, there are concerns that the metabolites arising from high doses of D-serine in humans may confer nephrotoxicity [19, 20]. Adding an inhibitor of DAAO with D-serine has been observed to increase the levels of D-serine in the plasma and central nervous system relative to D-serine administration alone in rats [21]. A potent inhibitor of DAAO is sodium benzoate, a commonly used food preservative and metabolite of cinnamon. To date there have been four published clinical trials using the compound for treatment of psychosis [22–25].

### Evidence for the effectiveness of sodium benzoate in psychotic illnesses

Lane et al. [22] published the first randomised clinical trial (*n*=52) of sodium benzoate for patients with chronic, stable schizophrenia, examining the effectiveness of 1000 mg/day adjunct sodium benzoate medication over 6 weeks. Those receiving sodium benzoate had greater improvements as measured by changes in the Positive and Negative Syndrome Scale (PANSS) total, PANSS positive, PANSS negative and PANSS general psychopathology with large effect sizes [22]. A second trial followed where 63 people with chronic schizophrenia were randomised to receive either combined sarcosine (2000 mg/day) and sodium benzoate (1000 mg/day), sarcosine only or placebo in addition to their usual antipsychotic therapy for 12 weeks. Those who received combined sarcosine and sodium benzoate had improvements in cognition and global functioning compared with those in the other groups [25]. A third trial of participants with treatment-refractory schizophrenia (*n*=60) examined the effect of 1000 mg and 2000 mg daily adjunct sodium benzoate for patients stabilised with clozapine over 6 weeks [23]. Both 1000 mg and 2000 mg groups significantly outperformed placebo in the Scale for the Assessment of Negative Symptoms (SANS) scores whilst only the 2000 mg group did better than those given placebo in total PANSS, Quality of Life Scale (QOLS) and Positive PANSS subscale [23]. This indicates a potential dose-dependent increase in efficacy of sodium benzoate. Finally, an RCT comparing adjunctive sodium benzoate (1000 mg/day) with placebo over 12 weeks for individuals with early psychosis (*n*=100) [26], most of whom had early schizophrenia (*n*=83) showed no significant difference in the change in PANSS scores between the two groups [24]. This lack of improvement from sodium benzoate relative to placebo may have been due to participants in both the intervention and control arms improving substantially over the duration of the trial because of the early illness which was treatment responsive. Alternatively, it may have been a result of insufficient sodium benzoate dose or another biological mechanism causing sodium benzoate to be more efficacious in people with chronic schizophrenia rather than early illness.

### Need for a dose-finding and mechanism of action trial

Uncertainty remains regarding the optimal sodium benzoate dose for the treatment of people with schizophrenia. The original dose-finding research was an open-label pilot study conducted on five participants where three received doses of 1000 mg/day and had reductions in PANSS scores. The other two received lower doses and showed no improvement [22]. This research informed the original trials that used 1000 mg/day [22, 25]. A subsequent trial reported that 2000 mg/day was more effective at reducing symptoms than 1000 mg/day, though it is not known whether further improvement can be achieved by doses greater than 2000 mg/day [23].

Likewise, uncertainty also exists regarding the mechanism of action through which sodium benzoate acts in psychotic illnesses [27]. The original hypothesis was that sodium benzoate increases the bioavailability of D-amino acids by inhibiting DAAO, which modulated the activity of the glutamate sub-unit of the NMDA receptors [22]. However, two recent trials have reported no changes in peripheral D-amino acid concentration following sodium benzoate administration [23, 24]. This could be the result of peripheral D-amino acid concentration not being reflective of brain D-amino acid concentration or that the dose of sodium benzoate was insufficiently high to achieve significant change. However, administration of sodium benzoate to mice who were injected with the NMDA receptor antagonist phencyclidine (PCP), attenuated the observed motor effects of PCP but did not result in changes in plasma or brain concentrations of D-serine [28]. Alternatively, reduction in oxidative stress has been  proposed as a potential alternate mechanism of sodium benzoate action [29], as oxidative stress has been associated with schizophrenia [30]. Lin et al. [23] observed an increase in peripheral catalase concentration of the 2000 mg/day sodium benzoate treated group relative to placebo and reported that catalase concentration was significantly negatively correlated with PANSS total and PANSS positive scores, congruent with evidence that red blood cell catalase is a state marker for schizophrenia [30]. Thus, we intend to examine the efficacy of sodium benzoate at three dose levels with the aim to clarify the efficacy and as well as to further examine the mechanism of action of sodium benzoate safety at the three doses.

### Safety profile of sodium benzoate

The safety of sodium benzoate has been studied extensively because it has been widely used as a food preservative, in cosmetics and also as a medication. The US Food and Drug Administration has classified sodium benzoate as ‘Generally Recognized As Safe’ and regulates the concentration of sodium benzoate to 0.1% by weight in food products and 1% concentration in medicines [31, 32]. The joint committee by the Food and Agriculture Organization of the United Nations and the World Health Organization has suggested an acceptable daily intake of 0.5 mg/kg of body weight [33].

The International Programme on Chemical Safety (IPCS) published a report on sodium benzoate (and a related compound benzoic acid) detailing the potential health effects of sodium benzoate in animal studies. Testing in rodents revealed a low rate of toxicity with mean lethal dose (LD50) values of > 1940 mg/kg body weight. Drawing evidence from two long term studies (12–16 months) in rodents, there was no evidence to suggest sodium benzoate had carcinogenic properties. Likewise, studies of the precursors of benzoic acid–benzyl acetate, benzyl alcohol, and benzaldehyde suggest that a carcinogenic effect of sodium benzoate is unlikely. The results of genotoxic activity were inconclusive in the IPCS report, and there were no consistent abnormal findings based on the Ames test. Based on in vitro studies of human lymphoblastoid cell lines, the evidence suggests that sodium benzoate at very high concentrations does have genotoxic effects. Sodium benzoate does have embryotoxic and fetotoxic effects; however, these are only evident at dosage levels high enough to cause severe maternal toxicity. A No Observable Adverse Effect Level (NOAEL) of approximately 1310 mg/kg body weight for teratogenic effects in rodents was established [34].

The acute toxicity of oral sodium benzoate in humans is low. There is evidence that some atopic individuals may be sensitive to food additives and preservatives (benzoate is a food preservative) [35]. The safety of sodium benzoate  reported in three trials of people with psychosisshowed no increase in reported side effects in participants who received sodium benzoate compared to placebo [22–24].

Sodium benzoate has been used since the late 1970s to treat patients with urea cycle enzymopathies that cause hyperammonaemia [36, 37]. The therapeutic dose administered to treat hyperammonaemia over several years is in the range of 250–500 mg/kg body weight per day, which equates to 17,500–35,000 mg per day for a body weight of 70 kg. It is noted that at this dose level, the clinical signs of toxicity are rare and are limited to anorexia and vomiting, especially after large intravenous bolus injections with 100% bioavailability.

### Objectives and hypothesis

The primary objective of the study is to determine the impact of 1000 mg daily, 2000 mg daily and 4000 mg daily of sodium benzoate treatment over 6 weeks on the total PANSS scores in patients with treatment-refractory schizophrenia compared to placebo.

The secondary objectives of the study are to determine the impact of (1000 mg daily or 2000 mg daily or 4000 mg daily) of sodium benzoate treatment over 6 weeks on the Positive and Negative Syndrome Scale (PANSS) subscales, Global Assessment of Function (GAF), Clinical Global Impression (CGI) and Patient Global Impression of Improvement (PGI-I), compared to individuals taking placebo. A further secondary objective is to determine the safety and tolerability of the three doses of sodium benzoate under investigation.

A tertiary (exploratory) objective is to determine the mechanism of action by examining the change in biochemical markers relative to baseline and correlate these with clinical outcomes. These biochemical markers consist of plasma amino acids (D-alanine, L-alanine, D-serine, glycine, glutamine and glutamate), plasma concentration of sodium benzoate, plasma catalase, 3-nitrotyrosine, malondialdehyde and high sensitivity CRP (hs-CRP).

It is hypothesised that participants allocated to the active arms (1000, 2000 or 4000 mg daily) will have a significant reduction in PANSS total score compared to the participants allocated placebo. This reduction is also expected in the secondary scores. It is also hypothesised that in the event of successful treatment with sodium benzoate, biochemical changes associated with the proposed mechanism of action will be observed, notably an increase in D-amino acids (D- and L-serine, D- and L-alanine, D- and L-glutamate) and decreased oxidative stress.

### Study design

The design is a randomised, placebo-controlled, double-blind parallel-group trial to determine the dose of sodium benzoate required for add-on treatment of patients with treatment-refractory schizophrenia. The study is a phase II dose-finding study with secondary endpoints which comprise a pharmacokinetic/pharmacodynamics investigation. This study will include 52 individuals with treatment-refractory schizophrenia. Patients will be given 1000 mg (500 mg bd), 2000 mg (1000 mg bd) or 4000 mg (2000 mg bd) daily of sodium benzoate or placebo. Participants will receive either active treatment (1000, 2000 or 4000 mg/day) or placebo in a 1:1:1:1 ratio. This study medication will be in addition to participants’ routine care, defined as ‘individualized combinations of psychopharmacology, behavioural interventions, rehabilitation and associated clinical services’ in keeping with Queensland Health standards of care. Face-to-face clinical assessments will be at baseline (week 0) and weeks 2, 4 and 6. Weekly phone contact will occur in weeks between face-to-face visits. The SPIRIT reporting guidelines have been used in this study protocol and a spirit checklist has been completed [38].

### Study population

Fifty-two (52) participants will be recruited through the mental health services at Metro North Hospital and Health Service and West Moreton Hospital and Health Services in Queensland, Australia. Recruitment to the study will be promoted by trial investigators working as clinicians in the study sites. This will ensure staff and consumers at the study sites are well informed about the study.

### Inclusion and exclusion criteria

Patients will be invited to participate in the study if they meet all of the following criteria:
Aged between 18 and 64 years (inclusive).Fulfil the DSM-IV criteria for schizophrenia, based on the Diagnostic Interview for Psychosis.Met diagnostic criteria for schizophrenia for at least 12 months duration.PANSS total score ≥70.Received antipsychotic medications for a period of at least one continuous month prior to assessment for the study and remained symptomatic despite the medications.Agreed to participate, has capacity to consent and is able to follow the study instructions and procedures.

Patients will be excluded from the study if they meet any one of the following criteria:
Known allergies to sodium benzoate (E211) or any part of the formulation of the investigational product.Suspected allergies or known adverse reactions to food preservatives in general.Unable to understand or communicate in English.For female participants, those currently pregnant, or planning to become pregnant or lactating during the study period or are sexually active and using ineffective contraception.Inability to follow the study instructions and procedures.

### Sample size justification

The primary analysis will be a mixed effect repeated measures analysis comparing total PANSS scores across 4 time points (baseline, 2, 4, and 6 weeks) across 4 dose groups (placebo, 1000 mg, 2000 mg and 4000 mg per day). A recent study by Scott et al. [24, 26] observed a standard deviation for total PANSS score of around 15 for all subjects, and closer to 10 for cases with baseline PANSS scores > 75. The autoregressive (AR(1)) correlation between weeks was estimated at 0.815. Assuming a decrease in PANSS scores similar to this previous study, this study has at least 80% power to detect an effect size of 0.55 between treatments with a sample size of 52 participants, incorporating an allowance for 20% attrition.

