### Clinical outcome measures

The severity of schizophrenia symptoms as measured by the Positive and Negative Syndrome Scale (PANSS) total score will be the primary continuous outcome measure. The mean change in scores from baseline to week 6 (end of the study) will be compared between study arms.

Average change in scores from baseline to week 6 (end of the study) in the following secondary clinical outcome continuous measures will also be included:
PANSS subscale scores, reflecting the severity of positive and negative symptoms and general psychopathology.Global Assessment of Function (GAF), a numeric scale (1 through 100) used by physicians to rate subjectively the social, occupational, and psychological functioning of adults.Clinical Global Impression (CGI) which is used to measure symptom severity, treatment response and the efficacy of treatments in treatment studies of patients with schizophrenia.Patient Global Impression (PGI) is a global index that is used to rate the response of a condition to a therapy (transition scale).

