### Statistical analysis

We will compare demographic and clinical differences between the groups at baseline (Fisher exact test for nominal variables and Mann-Whitney test or independent sample t test for continuous variables). All data will be analysed, regardless of whether participants withdrew spontaneously or were withdrawn by the investigator. Efficacy will be assessed according to standard Intention to Treat (ITT) analytic procedures (i.e. for those who do not complete the 6-week study period, we will carry forward their last observation on the study outcomes). A secondary analysis will also be conducted including participants who (1) were in the trial for all 6 weeks, (2) were treatment adherent ≥80% and (3) had no other major protocol violations. Missing values will be addressed using a mixed-effects model repeated measures analysis which is robust in maintaining statistical properties of tests. Mean changes in clinical assessment will be assessed using mixed-model repeated-measure (MMRM) methods with treatment, week, and treatment-week interaction as fixed effects and intercept as the only random effect; baseline value will be the covariant. *P* values will be based on 2-tailed tests with significance levels of 0.05 corrected for multiple comparisons. A more detailed statistical analysis plan will be finalised before database lock.

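### The sample size section describes a primary analysis that treats baseline as a compared time point, which does not fit the week-6 comparison set elsewhere, and no section says which model result decides

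*Protocol article*

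**What the plan says.** All references are to the protocol article.

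- **Sample size justification** opens with this sentence: "The primary analysis will be a mixed effect repeated measures analysis comparing total PANSS scores across 4 time points (baseline, 2, 4, and 6 weeks", and also across placebo and the three doses. Baseline is thus one of the four time points compared. The statement of at least 80% power for an effect size of 0.55 with 52 participants is attached to this analysis.
- **Clinical outcome measures:** for PANSS total, "The mean change in scores from baseline to week 6 (end of the study) will be compared between study arms".
- **Statistical analysis:** mean changes are assessed by a repeated-measures mixed model with "treatment, week, and treatment-week interaction as fixed effects and intercept as the only random effect", and "baseline value will be the covariant". Tests are two-tailed at "significance levels of 0.05 corrected for multiple comparisons". The section announces a more detailed analysis plan before database lock.
- **Objectives and hypothesis:** the objective is the effect of the three doses "on the total PANSS scores in patients with treatment-refractory schizophrenia compared to placebo". The hypothesis is that "participants allocated to the active arms (1000, 2000 or 4000 mg daily) will have a significant reduction in PANSS total score" relative to placebo.

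**The concern.** Three sections bear on the deciding comparison and do not agree on it. The clearest conflict is the role of baseline, which is an outcome time point in the sample size section and a covariate in the analysis section.

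That changes which term carries the treatment effect. With baseline among the outcomes, the arms start level, so a benefit that appears by week 2 and persists makes the group profiles diverge and shows in the group-by-time term. With baseline as covariate and weeks 2, 4 and 6 as outcomes, the same benefit is a constant shift. It shows in the treatment main effect and leaves almost nothing in treatment-week. Someone who carries the deciding term from one section into the model of the other tests the wrong thing. The main effect, averaged over visits, is also not the week-6 effect that the outcome section names.

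At stake are a clear statement of what the trial tests and a power figure that belongs to that test.

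**Working it through.** **Inputs from the protocol.** N = 52 allocated 1:1:1:1, so 13 per arm; 20% attrition, so 52 × 0.8 = 41.6 in total and 10.4 per arm; effect size 0.55, with d or f not stated; two-sided 0.05; AR(1) correlation 0.815 between weeks. Visits are two weeks apart, and 0.815 might apply per week or per visit, so both are used.

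**1. Reproducing the stated power.** Read 0.55 as Cohen's f in an overall four-group F test. The noncentrality is λ = f² × N = 0.3025 × 41.6 = 12.58, with 3 and 37.6 df and critical F about 2.85. Power is **0.817**, close to the stated figure. This reading is not stated in the text and does not use the AR(1) value.

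**2. Power for one dose against placebo at d = 0.55, 10.4 per arm** (normal approximation, 0.05 uncorrected).
- Unadjusted: δ = 0.55 × √(10.4/2) = 1.254, and Φ(1.254 − 1.960) = **0.24**.
- Adjusted for baseline: divide d by √(1 − r²), where r is the baseline-to-week-6 correlation.

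| r | source | adjusted d | δ | power |
|---|---|---|---|---|
| 0.29 | 0.815⁶ (per week) | 0.575 | 1.312 | 0.26 |
| 0.54 | 0.815³ (per visit) | 0.654 | 1.492 | 0.32 |
| 0.815 | taken directly | 0.949 | 2.164 | 0.58 |

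- At 0.05/3 the unadjusted value is 0.13 and the adjusted values are 0.14, 0.18 and 0.41.
- A noncentral t on 2 × 10.4 − 2 = 18.8 df gives slightly lower values at 0.05: 0.22 unadjusted and 0.24 to 0.54 adjusted.
- The unadjusted difference detectable with 80% power at 0.05 is (1.960 + 0.842) × √(2/10.4) = 1.23 SD.

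**3. Which term sees the effect.** Simulation of 4,000 trials per scenario, 13 per arm, complete data, unit SD, AR(1) 0.815 per week or per visit. ANCOVA and multivariate (Wilks) tests stand in for the mixed model. The effect is 0.55 SD in all three doses, constant from week 2.

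| Test | Per week | Per visit |
|---|---|---|
| Any dose v placebo at week 6, Dunnett, baseline as covariate | 34% | 43% |
| Treatment main effect, baseline as covariate | 45% | 59% |
| Treatment-week over weeks 2, 4, 6, baseline as covariate | 4% | 5% |
| Group-by-time over four time points, baseline as outcome | 23% | 41% |

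The last two rows are both interaction tests on the same data. They differ only in the role of baseline. The week-6 and main-effect verdicts differ in about 22–23% of these trials. With no effect, each test alone rejects at about 4–5%.

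The ordering depends on the shape of the effect. If it builds linearly to 0.55 SD at week 6 (per-week correlation, Bonferroni over three contrasts), power is 31% for week 6, 20% for the main effect and 10% for treatment-week.

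**The case against.** The strongest reply is that three of the four sections fit together. The objective compares doses with placebo, the outcome section sets change to week 6, and the model includes a treatment-week term, which is what allows a week-6 contrast to be estimated. Listing fixed effects does not nominate one of them as the deciding test. The sample size sentence may only describe the data layout, since it names no F test. This largely stands. Between the outcome and analysis sections there is under-specification, not contradiction. It does not cover the sample size sentence, which uses the words primary analysis and counts baseline among the compared time points.

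A reader might go further and infer an inflated false-positive rate. Claiming success on any of four candidate tests would give about 13–14% instead of 5%. No section contains such a rule, and each test alone holds its level. Choosing by result is also constrained, because analysts are blinded and the analysis plan is to be finalised before database lock.

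A reader might also fault the correction for naming no family or method. The method and the status of the secondary endpoints are ordinary content for the announced analysis plan and are not counted here.

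Finally, the simulation has no dropout, substitutes simpler tests for the random-intercept model, and uses chosen effect shapes. Its percentages are illustrative. That a constant shift disappears from treatment-week once baseline is a covariate does not depend on those choices.

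**Conclusion.** The point holds in a limited form. The sample size section's primary analysis does not match the week-6 comparison in the outcome section or the baseline-as-covariate model in the analysis section, and no section says which model result decides. The documents do not show that the trial would be called positive or negative at will, nor that the 5% error rate is broken.

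For a constant 0.55 SD effect, 13 per arm and complete data, power runs from about 5% (treatment-week) through 34–43% (week-6 contrasts) to 45–59% (main effect). The 80% is not shown to be miscalculated, but it reproduces only for an overall four-group test under an unstated reading of 0.55. For a single dose-versus-placebo contrast at d = 0.55 after 20% attrition, power is about 24% unadjusted and 26–58% baseline-adjusted, before correction for multiplicity. The width of that range reflects the unknown baseline-to-week-6 correlation.

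**What to change.** 1. In Sample size justification and Statistical analysis, state that the primary comparison is each dose against placebo in PANSS total change from baseline to week 6. It is to be estimated as week-6 contrasts from the repeated-measures model, with baseline as covariate and weeks 2, 4 and 6 as outcomes.
2. Apply the existing 0.05 correction to these three contrasts. State that the overall treatment test and the treatment-week test are descriptive.
3. Restate the power for this contrast, giving the effect-size metric and the assumed baseline-to-week-6 correlation, or say plainly that the 80% refers to an overall four-group test.

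The multiplicity method and the status of the secondary endpoints can stay with the analysis plan.

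**Cost.** This is wording only, before database lock, with no new data or patients. There are two real downsides. The stated power becomes less favourable once it refers to the dose contrasts. The overall and visit-averaged tests, which can be more powerful for an early effect, can no longer be used to claim success.

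### The stated 80% power for an effect size of 0.55 does not apply to the primary dose-versus-placebo contrast at week 6, where 0.55 SD has about 22–39% power; the metric behind 0.55 is not stated

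*Protocol article*

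**What the plan says.** The Sample size justification claims that "this study has at least 80% power to detect an effect size of 0.55 between treatments with a sample size of 52 participants". The total already contains a margin for one in five dropping out. The section describes a repeated-measures mixed model over four time points and four dose groups. It quotes a total PANSS standard deviation of about 15, or "closer to 10 for cases with baseline PANSS scores > 75", and an AR(1) correlation between weeks of 0.815. It does not say whether 0.55 is a standardised mean difference or another effect-size measure, which contrast and time point it refers to, or at what alpha.

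Elsewhere the article fixes what is to be compared:

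- **Study design:** "Participants will receive either active treatment (1000, 2000 or 4000 mg/day) or placebo in a 1:1:1:1 ratio".
- **Objectives and hypothesis:** the effect of each of the three doses "on the total PANSS scores in patients with treatment-refractory schizophrenia compared to placebo".
- **Clinical outcome measures:** mean change from baseline to week 6, compared between arms.
- **Statistical analysis:** "2-tailed tests with significance levels of 0.05 corrected for multiple comparisons", with baseline as covariate and a random intercept only. The correction method is not named.

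**The concern.** The phrase "an effect size of 0.55 between treatments", standing beside standard deviations, reads most naturally as about half a standard deviation between two arms. With 13 per arm, a difference of that size is far from 80% power.

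This matters most if the trial is null. A dose that fails to separate from placebo would be taken as well-powered evidence against a 0.55 SD benefit, when the trial had roughly a one-in-four to two-in-five chance of detecting it, and less after correction. For a dose-finding trial, that could lead to a useful dose being dropped.

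**Working it through.** **Inputs.** Total 52 in four equal arms (Study design): 52/4 = 13 per arm. Attrition 20% (Sample size justification): 52 × 0.8 = 41.6 evaluable, or 10.4 per arm. AR(1) correlation 0.815 (same section). Two-sided 0.05 (Statistical analysis). Assumption: the correction is Bonferroni over three doses, 0.05/3 = 0.0167.

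**Step 1: reproducing the stated figure.** Take 0.55 as Cohen's f in a one-way four-group F test, with noncentrality f² × N and 3 and N − 4 degrees of freedom.

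- N = 41: 0.3025 × 41 = 12.40, power 0.810.
- N = 41.6: 12.58, power 0.817.
- N = 42: 12.71, power 0.821.

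So the 80% reproduces with the stated attrition. The same f in a four-visit between-groups F test, with 0.815 treated as exchangeable, gives noncentrality 0.3025 × 41.6 × 4/(1 + 3 × 0.815) = 14.6 and power 0.875. This also meets the claim, but less closely.

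What f = 0.55 means in SD units:

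- two arms at each extreme: 2 × 0.55 = 1.10 SD apart;
- placebo against three equally effective doses: 0.55/√(3/16) = 1.27 SD;
- one arm at each extreme and two midway: 0.55 × √8 = 1.56 SD.

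**Step 2: each dose versus placebo at week 6, 0.55 as a standardised difference.** Noncentrality is 0.55/√(2v/n), where v is the variance left after baseline adjustment. The baseline to week-6 correlation is 0.815⁶ = 0.293 if 0.815 is per week, giving v = 1 − 0.293² = 0.914. If 0.815 is per two-week visit it is 0.815³ = 0.541, giving v = 1 − 0.541² = 0.707. Without adjustment v = 1. Example: n = 10.4, v = 1 gives 0.55/√(2/10.4) = 1.254.

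| Analysis (noncentral t) | df | n = 10.4, 0.05 | n = 10.4, 0.0167 | n = 13, 0.05 | n = 13, 0.0167 |
|---|---|---|---|---|---|
| Unadjusted two-sample | 2n − 2 | 0.222 | 0.109 | 0.270 | 0.142 |
| Baseline-adjusted, 0.815 per week | 4n − 5 | 0.248 | 0.129 | 0.301 | 0.166 |
| Baseline-adjusted, 0.815 per visit | 4n − 5 | 0.306 | 0.169 | 0.372 | 0.219 |

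The normal approximation adds one to two points; its last row is 0.320, 0.183, 0.385 and 0.234.

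**Step 3: most favourable pairwise case under AR(1).** Assume a constant effect from week 2, optimally weighted over three visits, with 0.815 per visit (v = 0.314). With 13 per arm and no correction, power is 0.688. With 10.4 per arm it is 0.586, and 0.404 at 0.0167.

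**Step 4: difference detectable with 80% power, 10.4 per arm (noncentral t).**

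- Alpha 0.05: 1.06 (per visit), 1.21 (per week), 1.30 SD (unadjusted). In PANSS points: about 11–13 at SD 10, 16–19 at SD 15.
- Alpha 0.0167: 1.24, 1.41, 1.54 SD. In points: about 12–15 at SD 10, 19–23 at SD 15.

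**The case against.** The strongest reply is that the article never calls 0.55 a pairwise standardised difference. It describes an analysis across four dose groups, and as Cohen's f for the omnibus test the figure is right. That stands: a reader might infer a plain arithmetic error, and the document does not support that. What remains on this reading is an unstated metric, a very large implied separation, and a powered test that is not the dose-versus-placebo comparison.

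A reader might also infer that no other reading reaches 80%. That is too strong. With AR(1) 0.815 per visit, 13 per arm and a constant effect optimally weighted over visits, all active doses pooled against placebo give 0.85. An omnibus test with two arms at each extreme of 0.55 SD gives 0.82. With the stated attrition these fall to 0.76 and 0.71, and neither is the week-6 contrast.

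The planned random-intercept model implies an exchangeable correlation. If 0.815 were used that way, pairwise power would be 0.56–0.66 at week 6 and 0.76–0.85 averaged over visits. The article labels 0.815 as AR(1), so this does not rescue the claim, but it shows how much depends on the covariance assumed. Similarly, if 0.55 were scaled to SD 15 while the outcome SD is 10, the difference would be 8.25 points, or 0.825 SD. Week-6 pairwise power would then be 50–71%, and a constant effect averaged over visits 75–92%. The text does not say this.

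Another tempting inference is that 52 is a per-arm size mistaken for a total, because 2 × (1.96 + 0.8416)²/0.55² = 51.9. That calculation contains no attrition, whereas the article's 52 includes it, so the coincidence is not evidence. Nor are the two quoted SDs an error: a standardised effect does not depend on them.

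Finally, 10.4 per arm is somewhat pessimistic, since participants who drop out still contribute their observed visits. The 13-per-arm columns bound that effect.

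**Conclusion.** The concern holds in a conditional form. For one dose against placebo at week 6, 0.55 SD has about 22–31% power after attrition and 27–39% without it, against the stated 80%. Under Bonferroni over three doses it is about 11–18% and 14–23%. No pairwise contrast under the stated AR(1) input, with 0.55 in units of the outcome SD, exceeds about 69%. The 80% is reproducible as Cohen's f for an omnibus test, but then the sentence reports power for an undisclosed metric and a test other than the stated objective. Either way the sentence needs correcting.

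The pairwise figures rest on three assumptions: 0.55 is a standardised mean difference, 0.815 is AR(1) per week or per visit, and the unnamed correction is Bonferroni over three comparisons.

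**What to change.** Restate the power sentence with the metric, contrast, time point, covariance assumption and alpha (including the multiplicity correction) behind 0.55. If it is Cohen's f for the omnibus test, say so and give the separation between arms that it implies.

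Then add, for each dose versus placebo at week 6:

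- the power the design has for 0.55 SD: about 22–39%, lower after correction;
- the difference detectable with 80% power after attrition: about 1.1–1.3 SD uncorrected, or about 1.2–1.5 SD if Bonferroni over three, also in PANSS points with the SD used and why it suits a population entering at PANSS 70 or above.

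The sponsor should settle the exact values once it confirms the covariance and correction. Present the dose comparisons as estimates with confidence intervals.

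The cost is wording in the protocol and analysis plan, and a less favourable statement of sensitivity. The sample size does not change.
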